## **DETAILED DESCRIPTION OF THE PROTOCOLS/INTERVENTIONS UTILIZED**

### **Intervention Overview:**

| Feature      | Description                                    |
|--------------|------------------------------------------------|
| Type         | Primary prevention                             |
| Duration     | Four weekly 60-minute sessions                 |
| Setting      | School classrooms during regular hours         |
| Facilitators | Trained peer educators (2 per group, total 50) |
| Group size   | 30 students per group (25 groups)              |

## ***Theoretical Foundation***

The intervention will be systematically developed based on the Theory of Planned Behavior, targeting each of the TPB constructs:

| TPB Construct    | Intervention Target                           | Activities                                                                          |
|------------------|-----------------------------------------------|-------------------------------------------------------------------------------------|
| Attitude         | Reduce favorable attitudes toward alcohol     | Discuss negative consequences, share personal stories, examine media messages       |
| Subjective Norms | Correct misperceptions about peer alcohol use | Present actual prevalence data, discuss social pressures, and role-play resistance. |

| TPB Construct                | Intervention Target                     | Activities                                                           |
|------------------------------|-----------------------------------------|----------------------------------------------------------------------|
| Perceived Behavioral Control | Enhance self-efficacy to refuse alcohol | Practice refusal skills, develop coping strategies, build confidence |
| Intention                    | Reduce intention to consume alcohol     | Set personal goals, make public commitments, develop action plans    |

## ***Curriculum Development Process***

The intervention curriculum will be developed through a multi-stage process:

### **Stage 1: Elicitation Study (December 2020)**

- Conduct an in-depth interview with 25 students (13 from the intervention and 12 from the control school)
- Explored salient beliefs about alcohol use
- Identified culturally relevant barriers and facilitators
- Informed content adaptation for local context

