## ***METHODS***

### ***Study Design and Setting***

A quasi-experimental pretest-posttest control group design with class-level allocation will be conducted from February to June 2021 in four public secondary schools in Dessie and Kombolcha towns, Northeast Ethiopia. This design was selected because individual-level randomization was not feasible due to the high risk of contamination within classrooms. Class-level allocation preserves the natural classroom environment, minimizes diffusion of intervention effects, and maintains logistical feasibility.

Dessie and Kombolcha towns are located in the South Wollo Zone of the Amhara National Regional State, approximately 400 kilometers northeast of Addis Ababa. The towns have a combined population of approximately 350,000 and serve as commercial and educational hubs

for the surrounding districts. The study will include public secondary schools offering grades 9-12.

This study protocol and the subsequent full report will adhere to the Transparent Reporting of Evaluations with Nonrandomized Designs (TREND) statement. A completed TREND checklist will be submitted as a supplementary file (S1 File) upon manuscript submission to ensure comprehensive and transparent reporting of all study elements,

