## *Sampling and Allocation Procedure*

**School Selection:** From the six eligible public secondary schools in Dessie and Kombolcha towns, four schools will be randomly selected using a computer-generated random number sequence. Two schools will be selected from Dessie and two from Kombolcha to ensure geographic representation.

**Class Selection and Allocation:** Within each selected school, classes in grades 9-12 will be stratified by grade level. From each grade, classes will be randomly assigned to either intervention or control arms using a computer-generated random sequence prepared by an independent researcher not involved in data collection. The allocation sequence will be generated prior to recruitment, and allocation concealment will be maintained by using

sequentially numbered, opaque, sealed envelopes to prevent selection bias. All students in selected classes will be invited to participate.

**Allocation Ratio:** 1:1 (intervention: control)

**Rationale for Class-Level Allocation:** This approach minimizes contamination between intervention and control participants, maintains logistical feasibility, and preserves the natural classroom environment.

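### The quasi-experimental label, the non-randomised reporting standard and a reference to a control school contradict the protocol's own random assignment of classes within schools

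*Protocol*

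**What the plan says.** Four parts of the protocol bear on how the arms are formed.

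- **Study Design and Setting** (and the Abstract, in similar terms): "A quasi-experimental pretest-posttest control group design with class-level allocation will be conducted". The reason given is that "individual-level randomization was not feasible due to the high risk of contamination within classrooms". The section also commits the protocol and final report to the "Transparent Reporting of Evaluations with Nonrandomized Designs (TREND) statement".
- **Sampling and Allocation Procedure**: "Within each selected school, classes in grades 9-12 will be stratified by grade level", and then "classes will be randomly assigned to either intervention or control arms using a computer-generated random sequence prepared by an independent researcher" who takes no part in data collection. The sequence is made before recruitment and concealed in sealed envelopes. Four schools are chosen, two per town, and the ratio is 1:1.
- **Stage 1: Elicitation Study (December 2020)**: 25 students are interviewed, "13 from the intervention and 12 from the control school".
- **Sample Size Determination** and the **GEE specification** under Between-Group Comparisons: both take the class as the cluster. School is not a clustering level and is not listed under Adjusted Variables. Grade is a covariate, but it is not in that list either.

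**The concern.** A trial in which an independent person generates a concealed random sequence and applies it to classes within school and grade is a stratified cluster-randomised trial. A quasi-experimental label and a checklist for non-randomised evaluations describe something else. A reader cannot tell whether a difference between arms may be attributed to the programme by virtue of randomisation, or only after arguing that confounding has been dealt with.

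The elicitation wording raises a different doubt, about the unit. Under allocation within schools there is no intervention school and no control school. If that phrase recorded the real arrangement, school would be confounded with arm, and both the sample size and the GEE would rest on the wrong unit.

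**Working it through.** **1. The plan's own sample size.** Inputs from Sample Size Determination: 36.8% against 26.8%, two-sided 5% (taken from the 95% confidence level), 80% power, design effect 2, 10% loss.

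- Per arm before clustering, pooled variance: (1.960 × √(2 × 0.318 × 0.682) + 0.842 × √(0.368 × 0.632 + 0.268 × 0.732))² / 0.10² = 339.3, rounded up to 340.
- 340 × 2 = 680, and 680 × 1.10 = 748 per arm, 1,496 in total. The stated figure is reproduced exactly.

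The figure rests wholly on clustering by class. (An ICC of 0.02 with 30 per class gives 1 + 29 × 0.02 = 1.58, not 2. That is a separate matter, and it makes the sample larger than its own inputs require.)

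**2. Which accounts does the class-level analysis fit?**

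| Account | Unit | Mechanism | Class-level GEE |
|---|---|---|---|
| Abstract; Study Design and Setting | Class | None stated; only individual randomisation ruled out | Right variance unit |
| Sampling and Allocation Procedure | Class, within school and grade | Concealed random sequence | Right variance unit |
| Elicitation Study, read literally | School | Not stated | Wrong unit |

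With classes as the unit and 680 analysed per arm, power is about 80% at a design effect of 2 (effective 680 / 2 = 340 per arm) and about 88% at 1.58 (680 / 1.58 = 430 per arm).

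**3. Hypothetical: whole schools as arms.** The protocol gives neither a split of schools nor a school-level correlation, so both are assumptions: two schools per arm, and a correlation ρ of 0.001 to 0.02 between students of the same school in different classes. The within-class correlation stays at the plan's 0.02, so ρ = 0.02 is the case where all of it is due to school. With 680 analysed per arm and 25 classes per arm (from the 25 groups in Intervention Overview), there are 680 / 25 = 27.2 students per class and 680 / 2 = 340 per school.

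- True design effect: DE = 1 + 26.2 × 0.02 + (340 − 27.2) × ρ = 1.524 + 312.8ρ.
- The class-level analysis assumes 1.524. Its type I error is P(|t| > 2.011 / √(DE / 1.524)) on 48 df.
- A school-level test has 2 df (critical value 4.303). Its power uses SE = √(0.4288 × DE / 680) for a difference of 0.10, where 0.4288 = 0.368 × 0.632 + 0.268 × 0.732.

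| Assumed ρ | DE | Type I error, class-level analysis | Power, school-level test |
|---|---|---|---|
| 0.001 | 1.84 | 7% | 38% |
| 0.005 | 3.09 | 16% | 26% |
| 0.01 | 4.65 | 26% | 20% |
| 0.02 | 7.78 | 38% | 14% |

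With literally one school per arm there are no degrees of freedom between schools, and no valid test exists.

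**The case against.** The strongest reply is that there is one procedure with a wrong label and one loose phrase. The sections that call the study quasi-experimental also say that allocation is by class, and they rule out only randomisation of individuals. Sampling and Allocation Procedure then supplies the mechanism. No section describes a non-random method; that is inferred from the label and the reporting standard. Most of this stands, and it rules out several stronger readings.

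- **That the class-level analysis is valid under only one account.** A reader might infer this, but class is the allocation unit under both the label and the detailed procedure. If classes were not randomised, the weakness would be confounding, not the level of clustering.
- **That whole schools were assigned.** The elicitation study is dated December 2020, before the protocol's date of January 15, 2021, and parts of it are in the past tense, so it may record schools already identified by arm. It is still one parenthesis about formative interviews, set against the Abstract, the design section, the sample size, the allocation section with its explicit rationale, and the GEE specification. The pilot's 30 students per school does not settle it, since those students are outside the main study.
- **That the 25 interviewees must be excluded.** They were interviewed about beliefs and did not test the curriculum as the pilot students do. They are at most 25 / 1,496 = 1.7% of the sample, and no bias from including them has been shown.
- **That the label causes the p < 0.05 rule for baseline imbalance.** That rule is a separate choice and does not depend on the design label.

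The reply does not remove the contradiction. The protocol still names a design class and a reporting standard that its allocation procedure contradicts, and it still refers to arm-specific schools that this procedure does not allow.

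**Conclusion.** The protocol is wrong as written on how the arms are formed. The contradiction follows from the text alone and needs no assumption. It matters because the design class determines how far the conclusion can be causal.

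Under the reading that most sections support, classes allocated within schools, the class-based sample size and the class-clustered GEE use the right unit and both stand. The inflated error of about 7% to 38% and the school-level power of about 38% down to 14% apply only if whole schools formed the arms. They depend on a two-against-two split and on school correlations that the protocol does not give. They show why the elicitation phrase has to be cleared up; they do not estimate a fault in the planned analysis.

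**What to change.** Confirm how the arms were formed and state it identically in the Abstract, Study Design and Setting, Sampling and Allocation Procedure, and the Elicitation Study.

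- **If classes were randomised as described:** call the study a stratified cluster-randomised trial with class as the unit and school and grade as strata. Add both strata to the GEE model. Report to the standard for cluster-randomised trials instead of TREND. Reword the elicitation study to say which schools the 25 students came from, without arm labels. The cost is text and two factors in the model; the sample size is unaffected.
- **If classes were allocated without randomisation:** keep the label and TREND, and rewrite Sampling and Allocation Procedure to describe what was done. The clustering unit stays, and confounding becomes the main limitation.
- **If whole schools were assigned:** rewrite Sample Size Determination, Sampling and Allocation Procedure and the GEE specification with school as the unit, and limit the conclusion to what four schools can support. This is costly, since more students in the same schools would not make up for having so few.

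In every case, add one sentence saying whether the 25 interviewees may enter the trial. Excluding them is not required.

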### **Stage 2: Literature Review**

- Reviewing existing peer-led alcohol prevention programmes
- Examining TPB-based intervention studies
- Identifies evidence-based strategies and activities

### **Stage 3: Expert Review**

- The curriculum will be reviewed by three public health experts.
- The curriculum will be reviewed by two school health educators
- The curriculum will be reviewed by two youth counsellors
- Modifications will be made based on feedback

### **Stage 4: Pilot Testing (January 2021)**

- A pilot test will be conducted with 60 students (30 per school) not included in the main study
- Assessed comprehension, acceptability, and feasibility
- Refined activities and materials based on feedback

## ***Peer Educator Selection and Training***

Peer educators will be selected based on demonstrated leadership qualities, effective communication skills, positive academic standing, and voluntary participation. A total of fifty students will be recruited and will undergo a comprehensive two-day intensive training programme prior to intervention delivery. The training content will include substance-related health and social consequences, principles of the Theory of Planned Behavior, behavior change communication strategies, facilitation techniques, ethical conduct, confidentiality, and interactive teaching methodologies.

The training will incorporate experiential components such as role-plays, rehearsal sessions, and scenario-based simulations to enhance competence and confidence. Two peer educators will be assigned to each intervention group to promote shared leadership, enhance session dynamics, and maintain implementation fidelity.

**Peer Educator Responsibilities:** Co-facilitate sessions with research team support; lead small group discussions; model positive behaviors; provide peer support; assist with activity implementation; and maintain confidentiality.

### ***Intervention Modules Summary***

| Module   | TPB
Targeted                    | Constructs         | Key Activities                                             | Duration |
|----------|------------------------------------|--------------------|------------------------------------------------------------|----------|
| Module 1 | Knowledge & Perception             | Risk               | Interactive presentation, small-group reflection, feedback | 60 min   |
| Module 2 | Attitudes & Skills                 | Coping             | Structured debate, relaxation training, feedback           | 60 min   |
| Module 3 | Subjective Norms & Decision-Making |                    | Guided discussion, decision-making practice, feedback      | 60 min   |
| Module 4 | Perceived Control & Efficacy       | Behavioral & Self- | Goal-setting, role-play refusal skills, feedback           | 60 min   |

### **Detailed Session Content**

#### **Module 1: Knowledge and Risk Perception (60 minutes)**

| Activity                 | Duration | Description                                                                 |
|--------------------------|----------|-----------------------------------------------------------------------------|
| Interactive Presentation | 35 min   | Health, psychological, and social consequences of alcohol; correcting myths |
| Small-Group Discussion   | 20 min   | Relate risks to real-life scenarios and share personal reflections          |
| Feedback                 | 5 min    | Complete session evaluation forms                                           |

**Objectives:** Increase knowledge of alcohol-related harms, correct myths about alcohol use, and understand short-term and long-term consequences.

**Expected Outcomes:** Understanding immediate and long-term health risks, recognition of harmful alcohol constituents, evaluation of benefits of abstinence, and strengthened intentions to remain alcohol-free.

## **Module 2: Attitudes and Coping Skills (60 minutes)**

### **Activity 1: Structured Debate (45 minutes)**

- Topic: "Is using alcohol good or bad for someone your age?"
- Procedure: Group assignment (5 min), argument development (15 min), debate preparation (5 min), debate session (10 min), reflection (10 min)

### **Activity 2: Relaxation Techniques (15 minutes)**

- Relaxation Exercise (5 min): Guided progressive muscle relaxation
- Deep Breathing (5 min): 4-count inhale, 8-count exhale (4-5 cycles)
- Homework: Practice daily

### **Activity 3: Feedback (5 minutes)**

**Objectives:** Challenge positive attitudes toward alcohol, develop negative attitudes toward harmful use, and understand personal values and goals.

**Expected Outcomes:** Enhanced negative attitudes toward alcohol, recognition of alcohol-free identity benefits, and acquisition of anxiety management techniques.

## **Module 3: Subjective Norms and Decision-Making (60 minutes)**

### **Activity 1: Guided Discussion (40 minutes)**

Discussion prompts regarding significant others (parents, other family members, close friends, teachers):

- Would they approve/disapprove of your alcohol use?
- How would they influence you?

- How would you influence them?
- What positive things do you do for family/friends/teachers?
- What positive things do they do for you?
- What actions have you taken to help others reduce alcohol use?

### **Activity 2: Decision-Making Practice (15 minutes)**

Based on Botvin (1980) 5-step model [27] :

1. Clarify the decision: What is the problem you are facing?
2. Consider possible choices: What options do you have?
3. Gather information: What else do you need to know?
4. Evaluate consequences: Advantages and disadvantages of each option?
5. Make and follow through: Which choice will you make?

### **Activity 3: Feedback (5 minutes)**

**Objectives:** Correct misperceptions about peer alcohol use, develop skills to resist peer pressure, and identify positive social influences.

**Expected Outcomes:** Recognition of social influences on alcohol decisions, enhanced problem-solving and decision-making skills, and development of coping strategies for peer/family pressure.

## **Module 4: Perceived Behavioral Control and Self-Efficacy (60 minutes)**

### **Activity 1: Goal-Setting and Barrier Analysis (30 minutes)**

Students identify goals, barriers, and strategies for:

- Own alcohol use
- Friends' alcohol use
- Parents' alcohol use

Guiding Questions:

- What have you done to control alcohol use in your life or support others?
- What are your personal goals for avoiding alcohol?
- What barriers might make it difficult to achieve these goals?
- How could you overcome these barriers?

### **Activity 2: Refusal Skills Role-Play (25 minutes)**

Part A: Identifying Peer Pressure Scenarios (10 minutes)

- Students share real or imagined pressure situations
- The facilitator lists scenarios on board
- Group discusses social dynamics and challenges

Part B: Role-Play Practice (15 minutes)

- Students practice assertive refusal skills, including a clear and confident "no", congruent body language and tone, offering alternative activities, and situation exit strategies

### **Activity 3: Feedback (5 minutes)**

**Objectives:** Build self-efficacy to refuse alcohol, develop action plans for high-risk situations, and make a public commitment to avoid alcohol.

**Expected Outcomes:** Development of practical resistance skills, increased confidence in handling peer pressure, clear personal goals for alcohol-free living, and strategies for overcoming barriers.

### **Intervention Fidelity Measures**

To ensure intervention fidelity, the following measures will be implemented:

- A facilitator manual with detailed step-by-step instructions for each session will be developed and provided to all peer educators
- Standardized materials, including identical presentations and activity guides, will be used across all intervention groups
- Research team members will be present at all sessions to observe and document implementation
- Ongoing supervision of peer educators will be conducted throughout the intervention period
- Fidelity checklists will be completed after each session to document adherence to the planned curriculum
- Debriefing meetings with regular feedback sessions will be held to address challenges and reinforce quality

### ***Control Group Conditions***

Control group students will continue with their regular school activities and receive standard health education as part of the existing curriculum, which covers general topics such as hygiene, nutrition, and disease prevention but does not specifically address alcohol use prevention or incorporate Theory of Planned Behavior principles. No alcohol prevention sessions will be provided to control participants during the study period.

To ensure ethical equity, control group students will be offered the complete intervention materials and a summary session after study completion.

# ***PLANS FOR OUTCOME ASSESSMENT AND DATA COLLECTION/ANALYSIS***

## **Outcome Measures**

### **Primary Outcomes**

| Outcome              | Definition                                                       | Measurement                                                                                               | Scoring                                        | Reliability/Validity                                                                                                                                                                                   |
|----------------------|------------------------------------------------------------------|-----------------------------------------------------------------------------------------------------------|------------------------------------------------|--------------------------------------------------------------------------------------------------------------------------------------------------------------------------------------------------------|
| Behavioral Intention | Motivation or plan to drink alcohol within the next three months | 3 items, 7-point Likert scale (very unlikely to very likely) [15, 28]                                     | Summed score 3-21; higher = stronger intention | Internal consistency will be considered acceptable if Cronbach's $\alpha \geq 0.70$ . Test-retest reliability will be considered acceptable if intra-class correlation coefficient (ICC) $\geq 0.75$ . |
| Current Alcohol Use  | Any alcohol consumption in the past 30 days                      | Single item: "In the past 30 days, on how many days did you have at least one drink of alcohol?" [29, 30] | Dichotomous (yes/no)                           | Test-retest reliability will be assessed using kappa statistic, with $\kappa \geq 0.60$ considered acceptable.                                                                                         |

